# The HYPERFlax trial for determining the anti-HYPERtensive effects of dietary flaxseed in newly diagnosed stage 1 hypertensive patients: study protocol for a randomized, double-blinded, controlled clinical trial

**DOI:** 10.1186/1745-6215-15-232

**Published:** 2014-06-18

**Keywords:** Hypertension, Flaxseed, Blood pressure, Nutrition, Alpha linolenic acid

## Abstract

**Background:**

In 2013 the World Health Organization deemed hypertension as a global crisis as it is the leading risk factor attributed to global mortality. Therefore, there is a great need for effective alternative treatment strategies to combat a condition that affects 40% of adults worldwide. Recently, the FlaxPAD Trial observed a significant reduction in systolic and diastolic blood pressure in hypertensive patients with peripheral arterial disease that consumed 30 g of milled flaxseed per day for one year. However, these patients were already on anti-hypertensive medication. Therefore, there is a need to assess if dietary flaxseed can effectively reduce blood pressure in the absence of peripheral arterial disease and anti-hypertensive medication in newly diagnosed hypertensive patients.

**Methods/Design:**

The HYPERFlax Trial is a parallel, superiority, phase II/III, randomized, double-blinded, controlled clinical trial. St. Boniface Hospital and the Health Sciences Centre of Winnipeg, Canada, will recruit 100 participants newly diagnosed with stage 1 hypertension who have yet to be administered anti-hypertensive medication. Participants will be randomly allocated with a 1:1 ratio into a flaxseed or control group and provided food products to consume daily for six months. At baseline, two, four, and six months, participant assessments will include the primary outcome measure, averaged automated blood pressure, and secondary measures: 24-hour food recall, international physical activity questionnaire, anthropometrics, and blood and urine sampling for biochemical analysis. Plasma will be assessed for lipids, metabolomics profiling, and molecules that regulate vascular tone. Urine will be collected for metabolomics profiling. With an estimated dropout rate of 20%, the trial will have a power of 0.80 to detect differences between groups and across time, out of an effect size of 0.7 (SD) at an α level of 0.05.

**Discussion:**

This trial will determine if dietary flaxseed is efficacious over six months as an anti-hypertensive therapy in subjects newly diagnosed with hypertension. If flaxseed can effectively reduce blood pressure as a monotherapy, then flaxseed will provide individuals on a global basis with a cost-effective food-based strategy to control hypertension.

**Trial registration:**

NCT01952340, Registered 24 September 2013.

## Background

In 2013 the World Health Organization highlighted that high blood pressure is a global crisis [1]. Hypertension was identified as the number one risk factor attributable to most deaths worldwide and accounted for 16.5% of deaths [1]. Globally, in 2008, 40% of adults aged 25 years or older had hypertension [1]. Many individuals live with undiagnosed, untreated, or uncontrolled hypertension and this can lead to cerebrovascular disease, dementia, stroke, retinopathy, myocardial infarctions, heart failure, coronary artery disease, renal disease, vision impairment, and peripheral arterial disease [1]. Therefore, it is imperative to identify more effective and desirable treatment options to reduce the burden of hypertension globally.

Dietary interventions have been suggested as a preferential complimentary strategy to current pharmacological strategies to control blood pressure [2]. Flaxseed is one dietary intervention that has been used recently to reduce the risk of cardiovascular disease. Flaxseed has exhibited cardioprotective effects in animal models predisposed to cardiovascular disease by reducing atherogenicity [3-5], plasma cholesterol [4,6], plasma glucose [6], plasma trans fats [5], and blood pressure [7].

In humans, patients with peripheral arterial disease (75% hypertensive) were administered 30 g of milled flaxseed per day for six months [8]. Flaxseed consumption resulted in a large decrease in systolic (-10 mmHg) and diastolic blood pressure (-7 mmHg) that was statistically different from the control group [8]. Blood pressure was inversely associated with plasma concentrations of two flaxseed bioactives, alpha linolenic acid (ALA), and enterolignans [8].

Despite the significant anti-hypertensive effects demonstrated in the FlaxPAD trial, the results contained some important limitations. Firstly, participants of the FlaxPAD trial were already on anti-hypertensive medication yet still exhibited poorly controlled blood pressure [8]. Therefore it is not possible to conclude if flaxseed can reduce blood pressure as a monotherapy or if it is only effective in conjunction with anti-hypertensive medication. Secondly, it remained unclear if flaxseed could effectively reduce blood pressure in hypertensive patients without coexisting peripheral arterial disease. Therefore, despite evidence showing the potential of flaxseed as a potent cardioprotective functional food, the efficacy of flaxseed as an independent treatment to reduce blood pressure in newly diagnosed patients with primary hypertension has yet to be investigated.

The hypothesis to be tested in the present study is: dietary flaxseed will reduce blood pressure in patients with newly diagnosed hypertension and will reduce the need for anti-hypertensive medication. In order to test these hypotheses, a phase II, randomized, double-blinded, controlled clinical trial called HYPERFlax has been designed. The acronym for the HYPERFlax trial stands for the anti-HYPERtensive effects of dietary Flaxseed. Parameters such as blood pressure, plasma and urine metabolomics, plasma lipid profiling, and plasma vascular tone regulators will be analyzed to assess the efficacy and mechanisms of action of dietary flaxseed in hypertension management.

The aims of the HYPERFlax trial are to:

1. determine if consuming 30 g of milled flaxseed daily can effectively reduce blood pressure over six months in newly diagnosed stage 1 primary hypertensive participants;

2. determine if dietary flaxseed is efficacious as a monotherapy;

3. determine if flaxseed can reduce the need for anti-hypertensive medication; and

4. identify the mechanisms of action responsible for the potential anti-hypertensive effects of flaxseed.

## Methods/Design

### Design overview

The HyperFlax trial is a parallel, phase II, randomized, superiority, double-blinded, controlled study with an allocation ratio of 1:1. The participants, study coordinator ([name]), nurse, overseeing medical doctor ([name]), principal investigator ([name]), and researchers will be blinded to the group designation. One individual that dispenses the food products will be aware of the group designation. The trial sponsor is St Boniface Hospital. The trial has received approvals from the Health Canada Natural Health Products Directorate (#192282), the University of Manitoba Research Ethics Board (B2013:079), the St Boniface Hospital Research Review Committee (RRC/2013/1324), and the Health Sciences Department of Research (R12014:048). The trial is registered at clinicaltrials.gov (NCT01952340).

### Settings and participants

The trial will take place at the Health Sciences Centre Hospital and St Boniface Hospital in Winnipeg (Manitoba, Canada). The aim is to enroll 100 participants. Based on the previous FlaxPAD trial [8] the expected attrition rate is 20%, which still allows for a power of 0.80 to detect differences between groups and across time, out of an effect size of 0.7 (SD) at an α level of 0.05. Participants will be recruited through doctor referral or in response to public advertisements and public screening booths. The inclusion and exclusion criteria below fit the criteria of individuals who are not recommended to be administered anti-hypertensive medication immediately according to the Canadian Hypertension Education Program Guidelines [9]. These individuals do not have a systolic or diastolic blood pressure of more than 160/100 mmHg and do not have diabetes or macrovascular target organ damage. The exclusion criteria, therefore, allow a period of time for lifestyle intervention, including new therapeutic strategies like dietary flaxseed, in low-risk hypertensive individuals.

Inclusion criteria includes:

1. stage 1 essential hypertension (average automated systolic blood pressure of 135 to 160 mmHg or diastolic blood pressure of 85 to 100 mmHg) [9];

2. Newly diagnosed; defined as being clinically diagnosed within the last six months. This includes being diagnosed at the screening examination;

3. Male or female;

4. Untreated by medications for hypertension;

5. 18 to 85-years-old and able to provide informed consent;

6. Females who are not pregnant and not planning on becoming pregnant during the course of the trial. A pregnancy test will not be administered for the trial;

7. Subjects who are receiving anti-platelet therapy must be on a stable dose for three months prior to the study;

8. Subjects who are receiving lipid-lowering drugs must be on a stable dose for three months prior to the study;

9. Subjects must have access to freezer space in their residence to hold up to one month of the frozen food products associated with this study.

Exclusion criteria includes:

1. Patients with ischemic pain at rest in limbs, ulceration, or gangrene.

2. Patient has undergone percutaneous coronary angioplasty, or has had coronary bypass within the last six months.

3. Known secondary hypertension of any etiology.

4. Patients with confirmed and clinically significant renal or hepatic abnormalities (creatinine >0.130 mM or creatinine clearance <45 ml/min, AST (aspartate aminotransferase) two to three times the rate, ALT (alanine amino transferase) > more than two to three times the normal consentration) and/or electrolyte imbalance serum K (potassium) + <3.5 or >5.5 mM;

5. History of major bleeding;

6. Patients with diabetes mellitus, bowel disease (including Crohn’s disease, celiac disease, colitis, peptic ulcer disease, irritable bowel syndrome, and diverticulosis), or other diseases such as active systemic lupus erythematosus, cancer, or end-stage respiratory disease;

7. Patients with macrovascular target organ damage, including cerebrovascular disease, stroke, dementia, hypertensive retinopathy, left ventricular dysfunction, myocardial infarction, renal disease, and peripheral artery disease;

8. Patients with clinical evidence of heart failure or an estimated life expectancy of less than two years or with a high baseline cardiac risk (post-ischemic or diabetic cardiomyopathy with an ejection fraction of less than 40%, Canadian Cardiovascular Society Class 3 or 4 angina or a need for coronary revascularization procedures);

9. Subjects that are on supplements other that those prescribed by their clinician for the entire duration of the study. Please see point 10 below;

10. Subjects ingesting more than two servings of fish per week, taking omega-3 fatty acid supplements, and/or consuming milled flaxseed or flax oil on a regular basis (more than or equal to 1 tablespoon of milled flaxseed or 1 teaspoon of flax oil per week). If the participant is willing, a four-week washout period eliminating these supplements may be allowed before entry into the trial;

11. Patients who have participated in an investigational drug program in the proceeding 30 days or who are unable or unwilling to comply with the protocol;

12. Subjects with allergies to any ingredient in the study product or placebo (including gluten);

13. Patients who will undergo surgery or intend to move outside Winnipeg during the trial period.

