All data will be stored without identifiable participant information in a password protected electronic document or locked cabinet. The final trial data set will be accessible only to researchers involved in the trial and any medical review board that requires access for safety purposes. In the likelihood of an unbalanced data set, absolute values will be analyzed with a mixed two-way repeated measures model with group and time as the between and within factor, respectively. A *post-hoc* comparison of the least squared means with a Tukey’s adjustment will be utilized to determine where the specific differences lie. Absolute change will also be calculated only for participants who provide clinical information and samples at all time points. Absolute change can be analyzed with one way analysis of variance (ANOVA) and the Kruskal-Wallis test, or multiple *t*-tests and the Mann Whitney U test with a false discovery rate correction. Multiple regression may be used to determine the influence of flaxseed on blood pressure while including factors such as age, BMI, gender, diet, or physical activity. Correlations will be utilized to determine relationships between biochemical markers and blood pressure. Subgroup analyses may also be performed, for example, the dichotomization of change in biochemical markers and observing subsequent change in blood pressure. All statistical tests will be set at a significance level of 0.05. Data will be published in peer-reviewed journals and discussed in public forums such as radio and television broadcasts.

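### The stated power of 0.80 is tied to no test or contrast: its inputs give 0.87 with a two-group t-test, and about 0.53 for one flaxseed-control contrast if Tukey's adjustment spans all eight group-by-time means

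*Protocol article*

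**What the plan says.** Under *Settings and participants* the protocol article states "The aim is to enroll 100 participants", gives an attrition figure ("the expected attrition rate is 20" per cent), and says this is a sample size "which still allows for a power of 0.80 to detect differences between groups and across time, out of an effect size of 0.7 (SD"), at alpha 0.05. The abstract repeats it: "With an estimated dropout rate of 20%, the trial will have a power of 0.80 to detect differences between groups and across time". Allocation is 1:1.

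Under *Statistical analysis* the leading analysis is a mixed two-way repeated measures model on absolute values, with group as the between factor and time as the within factor. A post-hoc comparison of least squares means with Tukey's "adjustment will be utilized to determine where the specific differences lie". The set of means that the adjustment covers is not given. Change from baseline may also be analysed, in participants with data at every time point, by several alternative tests. The section adds: "All statistical tests will be set at a significance level of 0.05".

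Blood pressure is the primary outcome. It is measured at screening, baseline, two, four and six months. The article singles out neither systolic nor diastolic pressure, and no visit.

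**The concern.** A power figure means something only for a stated test of a stated contrast. Here the article gives sample size, attrition, effect size and alpha, which is all that a simple two-group calculation needs, yet that calculation does not return 0.80. The claim speaks of differences between groups and across time, so the natural alternative is the mixed model. In that route, the only stated step that says where a difference lies is the Tukey comparison. A Tukey family built from every group-by-time cell consists mostly of pairs that do not address the trial's question, and each extra mean raises the critical value.

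If the conclusion on flaxseed against control at a given visit is drawn from that step, the power for it could be well below the figure given to readers and funders. If it is drawn from a plain contrast, the power is higher than stated. As written, nobody can tell which applies.

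**Working it through.** **Inputs from the article.** 100 enrolled, 1:1, 20% attrition: 100 × 0.80 = 80 completers, n = 40 per arm. Effect d = 0.7 SD. Alpha 0.05.

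**Assumptions.** Two-sided tests (sidedness is not stated). The SD is that of the quantity compared (the article does not say whether it is the SD of the absolute value or of the change).

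**1. Trying to reproduce 0.80 with a two-group test.** Noncentrality = d × √(n/2) = 0.7 × √20 = 3.13. The critical value t(0.975; 78 df) is 1.99. Noncentral t power:

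| Setting | Power |
|---|---|
| 40 per arm, 0.7 SD | 0.871 |
| 33 per arm, 0.7 SD | 0.800 |
| 34 per arm, 0.7 SD | 0.812 |
| 40 per arm, 0.634 SD | 0.80 |
| 40 per arm, 0.7 SD, alpha 0.025 | 0.799 |

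So 0.80 at 0.7 SD needs 33-34 completers per arm: 66/0.8 = 82.5, rounded up to 83 enrolled, to 68/0.8 = 85 enrolled. One-sided testing gives 0.93 and ignoring dropout gives 0.93, both further from 0.80. The figure does appear at alpha 0.025, but the article says 0.05 in both places.

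**2. Omnibus tests of the mixed model.** Four visits (baseline, two, four, six months), 40 per arm, compound symmetry. The within-person correlation r and the effect profile are assumed, because the article gives neither.

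- Group-by-time: noncentral F with 3 and 234 df, noncentrality (n/2) × Σ(δ_t − mean δ)² / (1 − r), where δ_t is the group difference at visit t in SD units.
- Group main effect: t-test on the person mean, whose variance is (1 + 3r)/4 in SD² units.

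| Profile | r | Group-by-time | Group main effect |
|---|---|---|---|
| Step (0.7 SD from month 2) | 0.3 | 0.78 | 0.92 |
| Step | 0.5 | 0.91 | 0.83 |
| Step | 0.6 | 0.96 | 0.79 |
| Linear (0.7 SD at month 6) | 0.3 | 0.63 | 0.61 |
| Linear | 0.5 | 0.79 | 0.50 |
| Linear | 0.6 | 0.88 | 0.46 |

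Values near 0.80 occur, as do values well above and well below it.

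**3. One same-visit contrast under Tukey.** Two groups × four visits = 8 means and 8 × 7/2 = 28 pairs. Three of these pairs compare the arms at the same post-baseline visit. The critical |t| is q(0.95; k, df)/√2, where k is the number of means. For k = 8 and 234 df this is 4.325/1.414 = 3.06, a per-comparison alpha of about 0.0025, against the same noncentrality of 3.13. The ranges below run from 78 df to effectively infinite df.

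| Means in family | Critical absolute t | Power at 0.7 SD |
|---|---|---|
| 2 | 1.99 to 1.96 | 0.87 to 0.88 |
| 4 | 2.63 to 2.57 | 0.69 to 0.71 |
| 6 | 2.92 to 2.85 | 0.58 to 0.61 |
| 8 | 3.11 to 3.03 | 0.51 to 0.54 (0.53 at 234 df) |

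With eight means and 40 per arm, 0.80 power needs (3.059 + 0.842)/√20 = 0.87 SD; at 0.7 SD it needs about 62 completers per arm.

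**4. A smaller corrected family.** Bonferroni over the three same-visit contrasts (alpha 0.05/3) gives 0.75 per contrast.

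**The case against.** A reader might infer that 0.80 fits no analysis in the plan. The document does not support that. The wording of the power claim suits the two-way model, and step 2 shows that its omnibus tests reach about 0.79 at ordinary correlations in two cases. The figure cannot be checked; it is not shown to be impossible.

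A reader might also infer that the trial has only an even chance of success. That goes too far, for three reasons. Tukey is described as post-hoc and is not named as the success criterion. Its family is not stated, so 0.53 is conditional on eight means. And 0.53 is the chance for one chosen visit: if 0.7 SD holds at all three post-baseline visits, the chance that at least one of them is significant under the eight-mean adjustment is about 0.83, 0.77 or 0.72 at correlations of 0.3, 0.5 or 0.7.

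The gap between 0.87 and 0.80 is on the safe side, because a sample with 0.87 power does still allow 0.80. Two blood pressure components sharing alpha would also explain 0.80 (0.799 at 0.025), though the text does not say so. Finally, a journal article condenses its protocol, and details of a sample-size calculation are often left out.

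All of this limits the point without removing it. The article itself fixes both a power figure and an adjusted comparison, and it does not connect them. An omnibus group or interaction test does not by itself say that flaxseed differs from control at six months, and the step offered for saying so can have far less power than claimed.

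**Conclusion.** The point holds in limited form. The power statement names no test or contrast and does not reproduce from its inputs with a two-group t-test (0.87, not 0.80, a conservative gap of 7 points). The omnibus mixed-model tests can match it only under correlations and profiles that the article does not give. If the conclusion rests on one same-visit Tukey contrast, power is about 0.53 with eight means, about 0.6 with six and about 0.7 with four; of the families in the table, only that of two means exceeds 0.80.

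These figures assume two-sided testing, 40 completers per arm, one blood pressure measure, and 0.7 in units of the SD of the quantity compared. The Tukey figures also depend on a family that the article leaves open. The finding is a mismatch between power claim and analysis, and does not show that the trial is too small: 80 completers are enough for a single pre-specified contrast.

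**What to change.** In *Statistical analysis*, name one primary contrast from the mixed model, flaxseed minus control at six months, tested at two-sided 0.05 and outside the Tukey family. Say which blood pressure measure it concerns, since the 0.87 applies to one measure at full alpha. Keep Tukey for secondary comparisons and state which means it covers.

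In *Settings and participants* and the abstract, restate the power to match: with 80 completers, about 0.87 for 0.7 SD, or 0.80 for 0.63 SD, two-sided alpha 0.05.

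If the primary conclusion is meant to rest on the eight-mean Tukey comparison, restate the power for one contrast as about 0.5. Limiting the adjusted family to the three same-visit contrasts is a weaker remedy: at about 0.75 per contrast under Bonferroni it does not restore 0.80.

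The cost is rewording of the sample-size and analysis paragraphs and the matching abstract sentence, with no extra participants. It should be done before any unblinded analysis.

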### Consent

Interested individuals will contact the study coordinator by telephone, upon which a pre-screening will be conducted to exclude participants based on the criteria above that can be determined over the phone. If the first criteria are met, a meeting will be scheduled to go through the consent and a secondary screening process will take place. Each participant will provide informed consent before the secondary screening process takes place. The study coordinator will again go through the exclusion and inclusion criteria to see if the participants are eligible for the study. Next, all study details will be outlined and the participants will be given a chance to ask any questions. If they consent to the study, the participant’s blood pressure will be measured six times within 10 to 15 minutes using a BPTru automated blood pressure machine BPTru, Coquitlam, BC, Canada to test if the participant has elevated blood pressure and meets the study criteria. The healthcare professional will also perform a brachial blood pressure measurement with a sphygmomanometer BPTru, Coquitlam, BC, Canada as is standard procedure at the doctors’ office. At this time, they will also see the lead medical doctor, [name], at the hypertension clinic at the Health Sciences Centre for an examination to exclude any macrovascular target organ damage. If the participants meet the inclusion and exclusion criteria they will be notified by telephone of their acceptance into the trial if they still choose to participate. Figure 1 details the study overview and design.

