### Participant assessments

#### **
*Averaged automated blood pressure*
**

The primary outcome measure is blood pressure. Blood pressure will be measured at a total of five visits: screening, baseline, two, four, and six months. A BPTru machine will be utilized to measure blood pressure six times within 10 to 15 minutes. The first reading will be discarded and the remaining five will be averaged. This measurement will take place in a quiet room while the participant is in a seated position and arm rested on an arm rest at heart level. A blood pressure reading with a sphygmomanometer and stethoscope will also be performed to ensure the congruency between this measurement and the automated measurement.

#### **
*Need for anti-hypertensive medication*
**

One of the secondary outcome measures is the need for anti-hypertensive medication. In the first two months of the trial the participants will not be prescribed anti-hypertensive medication as this is the lifestyle intervention period. A meta-analysis published in 2008 concluded the administration of a placebo to patients with hypertension for four to eight weeks provided no objective reason against safety [12]. At two, four, and six months the participants will have a blood pressure follow-up. The participants will be assessed for the need for anti-hypertensive medication. If deemed necessary, they will be prescribed anti-hypertensive medication according to the Canadian Hypertension Education Program guidelines. If prescribed anti-hypertensive medication, the type and dose of anti-hypertensive medication will be recorded. If a follow-up visit is required sooner than the two-month interval, the patient will be asked to return to the clinic for more visits as standard of care.

#### **
*Anthropometrics and questionnaires*
**

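### Inclusion criterion 1 admits people with one pressure above the 160/100 mmHg ceiling that the plan uses to justify withholding drugs

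*Protocol article*

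**What the plan says.** All of this is in the Protocol article.

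- **Entry rule.** Settings and participants, inclusion criterion 1, requires "stage 1 essential hypertension (average automated systolic blood pressure of 135 to 160 mmHg or diastolic blood pressure of 85 to 100 mmHg".
- **Population the rule is meant to capture.** The paragraph before the list says the criteria match people for whom guidelines do not recommend immediate drug treatment. It describes them as people who "do not have a systolic or diastolic blood pressure of more than 160/100 mmHg and do not have diabetes or macrovascular target organ damage". It then draws the conclusion: "The exclusion criteria, therefore, allow a period of time for lifestyle intervention".
- **Exclusions.** Number 6 begins "Patients with diabetes mellitus, bowel disease" and number 7 begins "Patients with macrovascular target organ damage, including cerebrovascular disease, stroke, dementia". Number 3 removes known secondary hypertension. None of the 13 states a blood pressure limit.
- **Screening.** Under Consent, the automated reading is taken "to test if the participant has elevated blood pressure and meets the study criteria". The stated purpose of the doctor's examination is to rule out target organ damage. People who meet the inclusion and exclusion criteria are then told they are accepted.
- **Consequence of entry.** Participant assessments, under the need for anti-hypertensive medication, states: "In the first two months of the trial the participants will not be prescribed anti-hypertensive medication as this is the lifestyle intervention period". If follow-up is needed before the two-month visit, "the patient will be asked to return to the clinic for more visits as standard of care".

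**The concern.** The introductory text and criterion 1 use the same upper figures, 160 and 100, but they do different work. In the introduction they are a ceiling on each pressure. In criterion 1 they are the upper ends of two alternative ranges, and meeting one range is sufficient. A person can therefore be eligible on one pressure while the other is above the ceiling.

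The ceiling is part of the plan's argument that it is acceptable to leave newly diagnosed people untreated for two months. Someone at 175/90 would be enrolled under the numbered criterion but would not be covered by that argument. This is first a question of participant safety and of a correct eligibility rule. There may also be an effect on the aims concerning monotherapy and the need for medication (Background, aims 2 and 3), if people above the ceiling are more often prescribed drugs from month 2. That is a reasonable inference, but no figure in the document supports it.

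**Working it through.** No sample size or power figure enters this point. The check is logical.

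**Inputs**, all from Settings and participants, with S the systolic and D the diastolic pressure in mmHg:

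- Criterion 1 as written: (135 ≤ S ≤ 160) or (85 ≤ D ≤ 100).
- Ceiling in the introductory text: S ≤ 160 and D ≤ 100.
- Criterion 1 with the ceiling added: both conditions together.

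**Step 1. Is each stated low-risk condition carried by a numbered criterion?**

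| Condition in the introductory text | Criterion that enforces it |
|---|---|
| Neither pressure above 160/100 | none |
| No diabetes | exclusion 6 |
| No macrovascular target organ damage | exclusion 7 |

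Two of the three conditions are enforced; the blood pressure condition is not.

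**Step 2. Apply the rules to particular readings.**

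| Reading | As written | Within ceiling | With ceiling added |
|---|---|---|---|
| 175/90 | pass (D in range) | no | fail |
| 145/108 | pass (S in range) | no | fail |
| 161/100 | pass (D in range) | no | fail |
| 160/101 | pass (S in range) | no | fail |
| 170/105 | fail (neither in range) | no | fail |
| 160/100 | pass | yes | pass |
| 150/92 | pass | yes | pass |
| 150/80 | pass (S in range) | yes | pass |
| 130/90 | pass (D in range) | yes | pass |

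**Step 3. Describe the gap.** The readings admitted against the ceiling form two regions:

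- S above 160 with D from 85 to 100;
- S from 135 to 160 with D above 100.

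The rule is also uneven: it refuses 170/105 but accepts 175/90, whose systolic pressure is higher.

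**Step 4. Does another step close the gap?** The screening reading is judged against the study criteria, so it inherits the wording of criterion 1. The medical examination has a different stated purpose. Recruitment includes public advertisements and screening booths, and a diagnosis made at the screening examination counts as newly diagnosed, so earlier medical triage cannot be assumed.

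**The case against.** The best defence is that the ceiling is in the document, unambiguous, and placed directly above the list it introduces. Criterion 1 asks for stage 1 hypertension, and the ranges in brackets only gloss that term. The gloss and the introduction cite the same guideline and use the same upper figures. Read together, 160 and 100 are limits, and the alternative only says which raised pressure can qualify a person. A rule that accepts 175/90 and refuses 170/105 is not one anybody intended. Every candidate also has six automated readings and a manual one, and sees a doctor at a hypertension clinic before acceptance. Randomization means that the gap does not by itself bias the comparison between groups. Finally, the screening form is not shown and may already carry the cap.

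Much of this stands. The intent is clear, the oversight makes unnoticed enrolment less likely, and the fault is one of drafting: the document does not set out to enrol people above 160/100. The provision for earlier visits also softens the risk after enrolment.

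It does not make the rule correct. The brackets hold the document's only numerical definition of stage 1, and that definition admits these readings. Acceptance is tied to the listed criteria, and the introductory sentence is not one of them. An earlier visit does not restore a limit at entry, and the two-month rule still says that no drug is prescribed. That the article condenses a fuller protocol is no answer either: it prints numbered criteria with thresholds, and one of them contradicts the paragraph introducing the list.

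**Conclusion.** The point holds. As written, criterion 1 does not deliver the population that the same section says it delivers. One of three stated low-risk conditions has no operative criterion, and two regions of blood pressure readings are admitted above the stated ceiling.

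The conclusion rests on the literal wording of criterion 1, on exclusions 1 to 13 containing no pressure limit, and on acceptance being decided by the listed criteria. It does not depend on any assumption about how screened people are distributed. The share who would fall in the gap is not given, and no effect on power, type I error or the treatment estimate is claimed. The correction is necessary because untreated people above the plan's own limit can meet the entry criteria.

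**What to change.** Add to inclusion criterion 1 that neither the systolic average may exceed 160 mmHg nor the diastolic average exceed 100 mmHg, and put the same check on the screening form if it is not there already. Keep the alternative between the two ranges. Replacing it with a requirement that both pressures be in range would wrongly exclude isolated systolic hypertension (150/80) and isolated diastolic hypertension (130/90).

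The cost is one clause in the criterion and one on the form. A few screened people with one pressure above the ceiling may no longer qualify, which could slow recruitment slightly; the document gives no number for this. They are people whom the plan's own rationale already places outside the trial.
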